#### Additional analyses

Predefined subgroup analysis will be done according to the presence of cholestasis. Logistic regression models will be used to test whether treatment effects differ significantly between these subgroups. Secondary endpoints will be compared using the Pearson’s chi-squared test or Mann-Whitney U test. Additionally, secondary endpoints will be analyzed separately using Cox regression analysis censoring patients no longer at risk and categorizing missing data as no event. For all other analyses, data will be considered missing at random. To evaluate differences in systemic inflammatory response after randomization, the APACHE-II, C-reactive protein levels, and presence of SIRS from randomization to day 7 will be calculated and compared between the treatment groups. To gain further insight into factors that are predictive of major complications or death after ERC, an exploratory analysis of the effects of (essential) baseline covariates (and potential interactions) will be performed using logistic regression analysis. The essential baseline covariates that will be studied are demographics, comorbidity, predicted severity prior to randomization, presence of organ failure prior to randomization, cholestasis, and duration of symptoms prior to randomization. In addition, the time between the start of symptoms and the ERC will be studied.

Direct medical and nonmedical costs and indirect costs will be compared to assess costs per patient with poor outcome (death or severe complications). Validated questionnaires will be analyzed to assess differences in the quality of life and provide input to compare costs per quality-adjusted life year (QALY). Health utility scoring algorithms for the EQ5D-5 L health status profiles available from the literature, based on preferences in the general population using time trade-off elicitation techniques, will be used to derive a QALY estimate for each patient. This QALY will be calculated as the product sum of health utilities and the lengths of the periods between the successive measurements [30, 31].

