### Follow-up

After hospital discharge, patients are seen at the outpatient clinic and further monitored at the discretion of the physician. After 1, 3, and 6 months, patients will receive a questionnaire (SF-36, SF-HLQ, and EQ5D-5 L, respectively) [26, 27]. A visit is scheduled at 3 months after randomization to identify persistent common bile duct stones or to detect endocrine or exocrine pancreatic insufficiency (serum liver and glucose measurements and fecal elastase).

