### Statistical considerations

#### Sample size calculation

The sample size calculation is based on a recent Dutch multicenter observational study of patients with biliary pancreatitis at high risk for complications [11]. The primary endpoint occurred in 32 % of the patients in which ERC was performed compared with 46 % of the patients who were treated conservatively. Taking into account that ERC was not always performed within 24 hours and that sphincterotomy was not routinely performed, a correction factor of 2 % for both percentages is added to both incidence rates. The APEC trial is a superiority trial in which the sample size calculation is based on the assumption that early ERC with sphincterotomy reduces the incidence of the primary endpoint by 18 % (48 % to 30 %). With a power of 80 %, a two-sided significance level of 5 % and a 1 % drop-out rate, a total of 232 patients are required to be included in the study (http://www.stat.ubc.ca/~rollin/stats/ssize/b2.html, accessed 20 July 2015)).

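### The additional Cox analyses of secondary endpoints count missing data as no event, which biases the hazard ratio if missingness differs between arms

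*Protocol article*

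**What the plan says.** Three consecutive sentences under Additional analyses in the protocol article set the rules.

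- The main comparison of secondary endpoints: "Secondary endpoints will be compared using the Pearson’s chi-squared test or Mann-Whitney U test".
- A supplementary Cox regression of the same endpoints: "censoring patients no longer at risk and categorizing missing data as no event".
- The default for everything else: "For all other analyses, data will be considered missing at random".

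The Secondary endpoints section lists each component of the primary composite as a secondary endpoint, so endocrine and exocrine insufficiency fall under the Cox rule. Under Follow-up, the only scheduled testing shown for these two is a single visit: "A visit is scheduled at 3 months after randomization to identify persistent common bile duct stones or to detect endocrine or exocrine pancreatic insufficiency". Other outpatient monitoring is left to the physician. The opening of Methods/Design states that patients and physicians cannot be blinded.

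**The concern.** The Cox sentence names two operations: one censors patients who are no longer at risk, the other assigns no event where data are missing. Read plainly, a patient whose status is unknown is entered as known to be event-free. That is correct only if none of these patients had the event. Cox regression has a standard way to use what is known and stop there, namely censoring at the last date of known status. The article sets this aside without giving a reason.

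The hazard ratio is at stake. The arm with more missing outcomes loses more events and looks better. In an open-label trial, attendance at the 3-month visit or return of a stool sample could differ by arm, and blinded adjudication cannot recover a test that was never done. In addition, each secondary endpoint with a Cox analysis is handled under two different missing-data assumptions, one in the Cox model and one in the chi-squared or Mann-Whitney comparison. The two results could then differ for reasons unrelated to treatment.

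**Working it through.** **Inputs from the article.** Sample size calculation: event rates of 48% (conservative) and 30% (early ERC), "With a power of 80 %, a two-sided significance level of 5 % and a 1 % drop-out rate", and 232 patients in total. Primary endpoint: a 180-day window. Randomization: 1:1.

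**Assumed inputs.** The article gives no missing fraction for any secondary endpoint. I use 1% to 20%, equal or unequal by arm, with missingness unrelated to the event.

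**Check of the plan's own figure.** For 48% vs 30%, with pooled variance and no continuity correction, the mean rate is 0.39 and

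n per arm = [1.960 × √(2 × 0.39 × 0.61) + 0.842 × √(0.48 × 0.52 + 0.30 × 0.70)]² / 0.18² ≈ 114.1, so 115.

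The total is 230, and 230 / 0.99 = 232.3, which agrees with 232. The article gives no figure for the effect of the missing-data rule, so this is derived below.

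**Outcome wholly missing and coded as no event.** This is the situation of a patient never tested for insufficiency. With true risk p and missing share m, the coded risk is q = p(1 − m). With roughly constant hazards over 180 days, HR ≈ ln(1 − q₁) / ln(1 − q₀), where 1 is early ERC and 0 is conservative treatment. The true values are ln(0.70) / ln(0.52) = 0.545 at the planning rates, and 1.0 with 30% in both arms.

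| Missing, ERC / conservative | Coded from 30% / 48% | HR (true 0.545) | Coded from 30% / 30% | HR (true 1.0) |
|---|---|---|---|---|
| 1% / 1% | 29.7% / 47.5% | 0.547 | 29.7% / 29.7% | 1.0 |
| 10% / 10% | 27.0% / 43.2% | 0.556 | 27.0% / 27.0% | 1.0 |
| 20% / 20% | 24.0% / 38.4% | 0.566 | 24.0% / 24.0% | 1.0 |
| 2% / 0% | 29.4% / 48.0% | 0.532 | 29.4% / 30.0% | 0.976 |
| 0% / 2% | 30.0% / 47.0% | 0.561 | 30.0% / 29.4% | 1.025 |
| 5% / 15% | 28.5% / 40.8% | 0.640 | 28.5% / 25.5% | 1.14 |
| 15% / 5% | 25.5% / 45.6% | 0.484 | 25.5% / 28.5% | 0.877 |

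The 2% vs 0% rows put the whole planned drop-out in one arm: 1% of 232 is 2.3 patients, and 2.3 / 116 = 2%. At the planning rates the shift is at most 0.561 − 0.545 = 0.016. With no true effect at 30% it is about 0.025.

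The planning rates belong to the composite and serve here only as an example, since single components will be rarer. With a true risk of 10% in both arms, 5% vs 15% missing gives 1.124 and the reverse gives 0.89, so the result depends little on the event rate.

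**Patient drops out part-way.** A simulation of 2,000,000 patients per scenario used exponential event times and drop-out at a uniform time in the window. It estimated the HR as the ratio of events per unit of follow-up.

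- Censored at last contact: 0.544 to 0.548 (true 0.545) and 0.996 to 1.000 (true 1.0), including the runs with unequal drop-out.
- Kept event-free to day 180, 5% vs 15% drop-out: 0.576 and 1.057.
- Kept event-free to day 180, 15% vs 5% drop-out: 0.519 and 0.942.

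Partial follow-up therefore gives a smaller bias than a wholly missing outcome, and censoring removes it when drop-out is unrelated to the event.

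**The case against.** The strongest reply is that coding a patient as having no event in a Cox data set means setting the event indicator to zero, which is censoring. If the time used is that of last contact, the sponsor already plans the proposed remedy, and the bias disappears under non-informative drop-out. The article does not state the censoring time, so this reading cannot be excluded. It is not the plain reading, however, because censoring is named separately for a different group of patients. Even on this reading the sentence needs the date.

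The second reply is that the only planning figure is 1% drop-out, at which the effect is negligible. That stands for loss of patients from the trial. It does not cover a patient who stays in the trial but is never tested for one component.

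A reader might infer more than the documents support:

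- **That the primary result is affected.** It is not. The primary analysis is an intention-to-treat chi-squared test and falls outside the Cox rule.
- **That the reported proportions and relative risks are understated.** For secondary endpoints these fit the chi-squared comparison, which is under missing at random. Only the Cox hazard ratios are exposed.
- **That the article contradicts itself.** The missing-at-random sentence is limited to the other analyses, so the Cox rule is an explicit exception, although an unexplained one. Two assumptions for one endpoint can also be informative if they are labelled as such.
- **That a large bias is to be expected.** Nothing in the article shows that attendance or testing will differ by arm.
- **That insufficiency is diagnosed only at the 3-month visit.** The definitions are in Additional file 3, which is not shown, and a diagnosis may arise in routine care. It can be said only that no other scheduled test appears.

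**Conclusion.** The point holds for the additional Cox analyses of secondary endpoints. Read plainly, the rule treats unknown status as known absence of the event, and the hazard ratio is biased whenever missingness differs by arm. The size rests on assumed missing fractions. With 5% vs 15% of outcomes wholly missing, a true HR of 1.0 becomes about 1.14, or 0.88 with the arms reversed. With equal missingness it stays at or near the truth (at most 0.566 against 0.545 at 20% missing). At the planned 1% drop-out, the shift is at most about 0.016 at the planning rates. All these figures assume roughly constant hazards and missingness unrelated to the event. Endocrine and exocrine insufficiency are the components most open to this. Severity is minor to moderate: the analysis is supplementary and the primary conclusion does not depend on it.

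**What to change.** In the Cox sentence under Additional analyses, replace the missing-data rule with censoring at the last date on which status for that endpoint is known. For endocrine and exocrine insufficiency, base the analysis on assessed patients under the missing-at-random assumption that the article already uses for its other analyses. Keep the present rule, if wanted, as a sensitivity analysis labelled as such. The chi-squared comparison cannot censor and need not change. Any imputation detail can be left to the statistical analysis plan.

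The cost is a sentence or two and a little programming. The date of last known status, or failing that of last contact, has to be taken from the case record forms. Censoring in turn assumes non-informative drop-out, so reporting the number unassessed by arm for each endpoint would let readers judge that assumption. The change should be settled before the unblinded final analysis.

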### Randomization

Patients are randomized to early ERC with sphincterotomy or to conservative treatment (1:1 ratio) with a web-based randomization module (ALEA, Academic Medical Center, Amsterdam, The Netherlands) in random blocks of two, four or six. At randomization, patients are stratified according to the presence of cholestasis and for region of the hospital. Cholestasis is defined as a serum bilirubin > 40 μmol/L at randomization or a dilated common bile duct (defined as > 8 mm in patients ≤ 75 years or > 10 mm in patients > 75 years).

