#### Descriptive statistics

The following patient characteristics before randomization will be described: age, sex, body mass index, comorbidity, American Society of Anesthesiologists (ASA) score, duration of symptoms before randomization, duration of symptoms before ERC, serum bilirubin levels, dilated common bile duct on ultrasound or computed tomography, presence of (multi) organ failure or systemic inflammatory response syndrome (SIRS), Sequential Organ Failure Assessment (SOFA) scale [28], Multiple Organ Dysfunction Score (MODS) [29], predicted disease severity according to APACHE-II, modified Glasgow, blood urea nitrogen, and C-reactive protein. Data will be presented in percentages for categorical variables. Continuous data with a normal distribution will be presented as a mean with standard deviation and as median with interquartile range in case of skewed distribution.

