#### Analyses

After 232 patients have completed their 6 months of follow-up, raw data regarding potential endpoints will be presented to an adjudication committee blinded to the treatment allocation to determine whether the endpoints meet the protocol-specified criteria. The study coordinator will blind the patient reports for treatment allocation. Each member of the committee will individually assess the potential endpoints. In case of dissenting opinions, a consensus meeting will follow. Only after consensus has been reached on each individual endpoint for each individual patient will a final analysis be performed by an independent statistician, unblinded for treatment allocation. Primary analysis, using the Pearson’s Chi-squared test, is based on the intention-to-treat principle, with patients being analyzed according to original treatment allocation, regardless of whether the cannulation or sphincterotomy was successful. For exploratory reasons a per-protocol analysis will be performed to compare treatment groups. A tabular listing of all patients excluded from the intention-to-treat populations will be provided together with the reasons for exclusion. Data will be presented as relative risks with 95 % confidence intervals. A two-tailed P < 0.05 is considered statistically significant.

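### The adjusted analysis of the primary endpoint is run only if baseline variables differ significantly, so chance decides whether this secondary estimate is reported

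*Protocol article*

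**What the plan says.** All references are to the protocol article.

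- **Secondary endpoints.** One listed item is a multivariable analysis of the primary endpoint, to be done if baseline variables differ significantly. The item names neither covariates nor a model.
- **Analyses.** The confirmatory test is unadjusted: "Primary analysis, using the Pearson’s Chi-squared test, is based on the intention-to-treat principle". The only significance threshold is given here: "A two-tailed P < 0.05 is considered statistically significant". Results are to be presented as relative risks with 95% confidence intervals.
- **Descriptive statistics.** This section lists the variables on which the arms could be compared: "The following patient characteristics before randomization will be described: age, sex, body mass index, comorbidity", followed by further severity, organ-failure and laboratory measures.
- **Randomization.** "At randomization, patients are stratified according to the presence of cholestasis and for region of the hospital".
- **Additional analyses.** Covariates are called essential here: "The essential baseline covariates that will be studied are demographics, comorbidity, predicted severity prior to randomization, presence of organ failure prior to randomization, cholestasis", with duration of symptoms before randomization completing the list. Their stated use is different: "To gain further insight into factors that are predictive of major complications or death after ERC, an exploratory analysis". Cholestasis also enters a model with treatment, as a subgroup test: "Logistic regression models will be used to test whether treatment effects differ significantly between these subgroups".

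**The concern.** In a properly randomized trial, a baseline difference between arms is due to chance. Its P value measures how unusual the imbalance is. It says nothing about whether the variable predicts the outcome, and only that prediction makes adjustment worthwhile. A rule that makes adjustment wait for a significant baseline difference therefore ties the analysis to the wrong quantity.

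Two things follow. Whether an adjusted estimate exists is settled only after the arms have been compared at baseline. And the covariates that the authors themselves call essential are not tied to an adjusted estimate of the overall treatment effect. If baseline balance is later questioned, readers will look for this analysis. They may find none, or one whose existence depended on a chance result in a variable with little bearing on outcome.

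**Working it through.** **1. The plan's own figure.** Inputs from Sample size calculation: 48% versus 30%, 80% power, two-sided 5%, 1% drop-out. With pooled variance and no continuity correction, the mean proportion is 0.39 and

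n per arm = [1.96·√(2·0.39·0.61) + 0.8416·√(0.48·0.52 + 0.30·0.70)]² / 0.18² = (1.352 + 0.571)² / 0.0324 ≈ 114.1, rounded up to 115.

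The total is 230, and 230/0.99 = 232.3, which agrees with the stated 232. Power at 115 per arm is 80.3%. The sample size belongs to the unadjusted test.

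**2. Chance that one variable triggers.** The 0.05 threshold is taken from Analyses and assumed to apply to the baseline tests. Under 1:1 randomization each test is significant with probability 0.05. In 6,000 simulated trials per setting (115 per arm, one normal covariate), the trigger rate was 4.7–5.3% for every assumed prognostic odds ratio per SD from 1 to 3. A strong predictor triggers no more often than an irrelevant variable.

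**3. Chance that any variable triggers.** Descriptive statistics gives 16 variables fixed before randomization, or 15 if organ failure and SIRS count as one item. Duration of symptoms before ERC is left out.

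| Assumption | P(at least one P < 0.05) |
|---|---|
| 16 independent variables | 1 − 0.95^16 = 56% |
| 15 independent variables | 1 − 0.95^15 = 54% |
| All 16 correlated at 0.3 | about 48% |
| 8 correlated at 0.5, 6 independent, 2 that cannot trigger | about 45% |
| 8 correlated at 0.7, 6 independent, 2 that cannot trigger | about 41% |
| 10 effective independent tests | 1 − 0.95^10 = 40% |
| 6 effective independent tests | 1 − 0.95^6 = 26% |

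The two that cannot trigger are bilirubin and bile duct dilation. They define cholestasis, a stratification factor, so their imbalance is restrained. SOFA, MODS, APACHE-II, Glasgow, urea nitrogen and C-reactive protein overlap, so the lower rows are more plausible than the first two. The article gives no correlations; those above are assumptions.

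**4. What the adjusted estimate forgoes.** Prognostic strength is not in the article either. The same simulation, with true risks of 48% and 30%, gives the following power.

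| Assumed odds ratio per SD | Always-adjusted logistic test |
|---|---|
| 1.5 | 82% |
| 2 | 84% |
| 2.5 | 86% |
| 3 | 87% |

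The unadjusted test has 80–81% throughout. Adjusting only when this one covariate's baseline test is significant, and otherwise not, also gives about 80–81%. With no treatment effect, always adjusting for a covariate with odds ratio 1.5–3 rejected in 4.5–4.9% of trials (simulation error about 0.3 points). These figures describe the information in an adjusted analysis, not the power of the trial's primary test.

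**5. Feasibility.** Expected events are about 116 × 0.48 + 116 × 0.30 = 55.7 + 34.8 ≈ 90. Treatment, cholestasis and five further single-term covariates make seven terms, or about 13 events per term before region is added. The article does not say how many regions there are.

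**The case against.** The strongest reply is that little depends on this item. The confirmatory test is a fixed, unadjusted chi-squared test, and the sample size is built on it. The multivariable analysis is secondary, so its trigger cannot change the primary test's type I error or power. That stands. A reader might infer from the simulated gains that the trial loses several points of power. It does not: the primary test has about 80% power under the design assumptions with or without the proposed change.

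A second reply is that the item says when to adjust, not for what. A reader might infer that only variables with P < 0.05 enter the model, so that the model would usually contain irrelevant covariates and miss near-significant predictors. The article does not say this. Once triggered, the model could use the essential covariates, and an unshown full protocol or analysis plan may list them. Any figure for how often the model would be filled with irrelevant variables would rest on that unstated rule and on an arbitrary share of prognostic variables. The trigger, however, is stated in the article, so the point does not depend on something left to another document.

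Third, it would be too broad to say that the essential covariates play no part in any treatment analysis. Cholestasis enters the subgroup test, and the exploratory regression allows for interactions. Neither is an adjusted overall effect.

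Finally, the trigger could be defended as a safeguard against a bad imbalance. An analysis that is always run covers those same trials, and also the imbalances in strong predictors that fall short of significance.

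**Conclusion.** The point holds, and it is limited to the secondary analysis. Making the adjusted analysis conditional on significant baseline differences is a flawed stated rule: each variable triggers with probability about 5%, whatever its prognostic value. Overall, an adjusted estimate would be reported in at most 54–56% of trials under independence and in roughly 26–45% with substantial overlap. This rests on the 0.05 threshold applying to the baseline tests and on the listed variables being the ones tested.

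The consequence is an adjusted estimate that is absent or triggered by chance, together with the precision that a prespecified adjustment would bring. The size of that precision gain cannot be fixed from the article. The primary result, its error rate and the sample size of 232 are not in question. The change is worth making because it is simple and nearly free, not because the trial's main conclusion is at risk.

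**What to change.** Replace the conditional item under Secondary endpoints with text such as: *The primary endpoint will also be analysed with adjustment for cholestasis, hospital region, age, comorbidity, APACHE-II score, organ failure before randomization and duration of symptoms before randomization, whatever the observed baseline balance. The result will be reported as an adjusted relative risk with 95% confidence interval.*

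The first two covariates are the stratification factors. The others are an example of a short list from the essential set, and the authors may choose differently (sex, for instance, also belongs to demographics), provided the choice rests on expected prognostic value. State how the relative risk is obtained, for example by standardization from a logistic model. Drop baseline significance testing as a trigger and keep the chi-squared test as primary.

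The list should be fixed before unblinding, by people who have not seen outcomes by arm, including any interim results. The cost is a sentence or two in the plan. The clinical covariates are already among the described baseline data and region is known from randomization. The one real burden is a stated way to handle a few missing baseline values.
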